#### Intention to treat (ITT) approach

A full-information maximum likelihood approach for an intent-to-treat analysis is used, and a Monte Carlo simulation with 10,000 replications suggests we will be able to detect a minimum standardized effect of 0.30 with a probability of correctly rejecting a false null (power) of .81. If the recruitment rate is closer to 3 per week resulting in a sample of *N* = 468, the minimum detectable standardized effect is 0.25. By including additional control variables (all ES’s = .10), the minimum detectable effect sizes decrease to 0.27 and 0.22, respectively. A recent and relevant meta-analysis reported effect sizes for exercise intervention effects on similar outcomes ranging from ES = 0.30 to ES = 0.84 [30]. We will compare the mean differences between groups and the rates of change (slopes) between the groups.

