## Methods/design

### Study design

A two-group, 16-week randomized clinical trial is designed to address persistent taxane-induced peripheral neuropathy in women treated for invasive breast cancer. The study design is a parallel, two-arm, randomized controlled trial with a 1:1 ratio between groups.

A sample of 312 women who completed taxane-based chemotherapy for breast cancer and have symptomatic neuropathy (≥ 3 on a neuropathy visual analog scale VAS) ≥ 6 months following completion of taxane-based chemotherapy will be recruited. Participants are randomized to either a Home-Based Physical Activity Intervention (B-HAPI) for persistent taxane-induced neuropathy or an educational attention control group. Assessment of gait, balance, strength of lower extremity muscles, neuropathy symptoms, and nerve conduction velocity will be collected at baseline (prior to randomization) and 16 weeks. The participant flow diagram is shown in Fig. 1. The protocol follows the Standard Protocol Items: Recommendations for Interventional Trials (SPIRIT) Figure (Fig. 2) and Checklist (Additional File 1) [16].

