### Sample size

Power analyses were performed through a Monte Carlo simulation approach with the software Mplus [28, 29]. Observations were spaced at 0 and 16 weeks, with the number of weeks since baseline as the time metric to evaluate the efficacy of the 16-week intervention.

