#### SEM approach

The variance population parameters recommended by Muthén and Muthén were used (intercept variance = 0.50, slope variances (intervention = 0.10, intercept and slope covariances = 0.00), and residual variance at all waves = 0.50). Homogeneity of variances was assumed between the treatment and control groups. To reflect effective randomization of participants to conditions, we modeled no mean difference between treatment and control conditions at baseline. The differences in slopes between the treatment and control conditions during the intervention period are the focal parameter to be adequately powered. Given alpha = .05, a two-tailed hypothesis test, and the view that a power value of .80 will be adequate to detect a treatment effect, a minimum sample of *N* = 312 participants (based on recruitment of 2 or more participants per week for 3 years) with 20% attrition and 10% periodic non-response, is needed.

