## Trial status

This study protocol version number is 2, dated March 12, 2022. The recruitment of participants started in August 2020. Currently, there are 33 participants recruited (17 in the intervention group and 16 in the control group). Recruitment is estimated to be completed in July 2024.

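### The stated power of .81 at a standardized effect of 0.30 does not follow from the plan's own two-wave inputs once its own 20% attrition and 10% non-response are applied

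*Protocol article*

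**What the plan says.** All of this is in the protocol article, under Sample size unless stated.

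- **Design of the simulation:** "Observations were spaced at 0 and 16 weeks". Under Study design, baseline is taken before randomization, so week 16 is the only measurement after it.
- **Test and target** (SEM approach): "Given alpha = .05, a two-tailed hypothesis test", with the view that "a power value of .80 will be adequate to detect a treatment effect".
- **Variance inputs** (SEM approach): intercept 0.50, slope 0.10, intercept-slope covariance 0, residual 0.50 at each wave, and no group difference at baseline. The group difference in slope is named as the focal parameter.
- **Losses:** the 312 is given "with 20% attrition and 10% periodic non-response, is needed".
- **Result** (Intention to treat approach): with FIML and 10,000 replications, the trial is said to be "able to detect a minimum standardized effect of 0.30 with a probability of correctly rejecting a false null (power) of .81". For N = 468 the detectable effect is given as 0.25, and with extra covariates as 0.27 and 0.22.
- **Accrual:** the 312 is "based on recruitment of 2 or more participants per week for 3 years". Trial status, which places the end of accrual in 2024, reports: "Currently, there are 33 participants recruited (17 in the intervention group and 16 in the control group). Recruitment is estimated to be completed in July".

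**The concern.** The section prints nearly everything needed to check its headline figure. With one post-baseline visit, a loss of 20% plus 10% removes over a quarter of the information on the treatment contrast. Yet the stated power is about what 312 complete pairs would give under one plausible reading.

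The figure matters because 0.30 is also the lower end of the effect range (0.30 to 0.84) that the plan takes from a meta-analysis. The plan therefore claims adequate power across that whole range. On its own inputs, the chance of missing a true effect of 0.30 would be about 28% to 43% rather than 19%, and a null result would be read with more confidence than the calculation supports.

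**Working it through.** **Implied moments, time coded 0 and 1**

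- Baseline variance = 0.50 + 0.50 = 1.00
- Week-16 variance = 0.50 + 0.10 + 0.50 = 1.10
- Covariance = 0.50, so correlation = 0.50/√1.10 = 0.48
- Variance of change = 1.00 + 1.10 − 2(0.50) = 1.10
- Baseline-adjusted residual variance = 1.10 − 0.50²/1.00 = 0.85

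With two waves, the slope difference is the difference in change. With equal baseline means imposed, FIML is in effect the baseline-adjusted analysis.

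**Pairs.** None lost: 312. Attrition only: 312 × 0.80 ≈ 250. Both losses at week 16: 312 × 0.80 × 0.90 ≈ 225.

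**Formula.** For 1:1 allocation, SE = √(4 × variance / pairs). Power is two-sided at .05 from the noncentral t distribution. The effect is 0.30 if standardized to the baseline SD, or 0.30 × √1.10 = 0.315 if standardized to the week-16 SD.

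**The plan's figure first.** With 312 complete pairs, baseline adjustment and the baseline SD, SE = √(4 × 0.85/312) = 0.1044 and 0.30/0.1044 = 2.87, which gives power .82. That is close to .81, but with no loss.

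**With the losses.** For 225 pairs, the baseline-adjusted SE = √(4 × 0.85/225) = 0.1229, ratio 2.44, power .68. For change, SE = √(4 × 1.10/225) = 0.1398, ratio 2.15, power .57.

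| Pairs | Adjusted, baseline SD | Adjusted, week-16 SD | Change, baseline SD | Change, week-16 SD |
|---|---|---|---|---|
| 312 | .82 | .85 | .71 | .75 |
| 250 | .73 | .77 | .62 | .66 |
| 225 | .68 | .72 | .57 | .61 |

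A 10,000-replicate simulation of the two-wave model agrees. With the baseline SD it gives .825, .725 and .684 adjusted, and .723, .625 and .572 for change.

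**What FIML adds.** If baseline means are left free, the baselines of participants without week 16 still contribute. The variance of the change contrast is then 2 × [0.85/(pairs/2) + 0.25/156]. For 225 pairs SE = 0.1353, and power is about .60 (baseline SD) or .64 (week-16 SD). FIML cannot exceed the baseline-adjusted column.

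**Time coded in weeks**, the metric that the plan names. Week-16 variance = 0.50 + 256 × 0.10 + 0.50 = 26.6, and adjusted residual variance = 26.6 − 0.25 = 26.35. With the week-16 SD, power is .76 with 312 complete pairs, .66 with 250 and .61 with 225. Standardizing to the slope SD gives .74, .64 and .60.

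**N = 468.** 0.30 × √(312/468) = 0.245, so the stated 0.25 is consistent with simple rescaling of the same result. With both losses (about 337 pairs), the detectable effect at .80 power is 0.27 to 0.28 adjusted and 0.31 to 0.32 for change.

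**Sensitivity to the correlation** (an assumption; unit variances, 225 pairs, effect 0.30):

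| Correlation | Adjusted | Change |
|---|---|---|
| 0.5 | .73 | .61 |
| 0.6 | .80 | .71 |
| 0.7 | .88 | .82 |

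**Accrual.** 2 per week × 156 weeks = 312. August 2020 to 12 March 2022 is 80 to 84 weeks, so 33 recruits is about 0.4 per week. The remaining 279 over about 125 weeks to the end of July 2024 need about 2.2 per week.

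**The case against.** The strongest reply is that the variance inputs are generic simulation defaults, not estimates for these outcomes. They imply a baseline-to-week-16 correlation of only 0.48, whereas Table 4 reports test-retest correlations of 0.70 to 0.97. Short-interval reliability is only an upper guide to a 16-week correlation. Even so, at 0.6 the baseline-adjusted analysis reaches about .80 after both losses, and at 0.7 the change score does too. This stands: the trial may well have adequate power. It does not rescue .81 as the result of the inputs the plan reports.

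It is also fair that the standardizing SD and the Mplus code are not shown, and that placing all of the 10% non-response on week 16 is an assumption. The checks above vary the SD, and dropping the 10% altogether still gives at most .77. A one-sided test could give about .81 under some variants, but the plan states two-tailed. The covariate gains are reported separately and are not part of the .81.

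A reader might infer that the simulation left out the missing data, or used more waves than the trial has. The documents do not show either. The match at 312 complete pairs holds for one combination of SD, time coding and model. With the week-16 SD, about 278 pairs would suffice for .81, which allows roughly 11% loss.

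**Conclusion.** The point holds in this form: the reported power is wrong for the reported inputs. With two waves, the printed variances, two-tailed .05 and both losses at week 16, power at 0.30 is about .68 to .72 baseline-adjusted and .57 to .61 for the change contrast in complete pairs (.60 to .64 with FIML). No two-sided reading tried reaches .80 under the stated losses, even with the 10% left out.

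Two stronger conclusions are tempting and not supported. One is that the trial is underpowered for 0.30. That depends on the true baseline-to-week-16 correlation, which the documents do not give. The other is that slow recruitment invalidates the sample-size calculation. The rate of about 0.4 per week against at least 2 makes the July 2024 forecast doubtful, but it is a feasibility matter separate from power at N = 312. It also assumes that the count of 33 refers to about the version date.

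**What to change.** Re-run the simulation with exactly two waves, the stated losses at week 16, and the analysis model that will be used. State which SD standardizes the effect and how time is coded. Show power over a range of baseline-to-week-16 correlations, with a reason for the one chosen. Then replace .81 at 0.30, 0.25 at N = 468, and the covariate-adjusted 0.27 and 0.22 with whatever the re-run gives. The figures above are a check and should not be printed in its place.

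Separately, reconcile the premise of at least 2 recruits per week with the 33 reported and the July 2024 completion date.

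The cost is one re-run and rewording of the sample-size and status paragraphs. The stated power will be less favourable if the present inputs are kept. No extra patients are needed for the correction.

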### Assignment of interventions: allocation and blinding

Randomization to study groups is achieved using a computer-generated random numbers list (REDCap software, Nashville, TN) by the study statistician. A sealed, consecutively numbered, opaque envelope containing the subject’s group assignment (Exercise Intervention or Educational Attention Control) is opened to reveal the participant’s study group assignment. The study statistician generates the allocation sequence. The project manager enrolls participants, and the research assistant assigns participants to intervention groups. It is not an open-label study. The PI, data collectors, and the principal statistician are blinded. The data collector is blinded to the study group assignment. There is no unblinding procedure. No blocking or stratification is used.

## Data collection, management, and analysis

### Assessment and collection of outcomes

The assessment of gait, balance, and lower extremity muscle strength is performed by personnel with Master of Science in Kinesiology trained to perform these assessments. In addition, the assessment of neuropathy symptoms patient-reported questionnaire and the nerve conduction velocity are performed by a member of the research team and a neurologist, respectively. Outcomes are collected at baseline and at 16 weeks to provide baseline and end of intervention data. These data collection points reflect current knowledge concerning the impact of exercise on gait, balance, and lower extremity muscle strength from pre- to post-intervention [31–34]. The outcomes assessment occurs at the Human Functional Performance Laboratory at the University of South Florida.

### Assessment of gait

The APDM Opal (Mobility lab v1, APDM, Inc., Portland, OR) inertial measurement units (IMU) are used to assess gait. The APDM IMUs are wireless sensors for measuring motion that allows clinicians to perform gait assessments quickly [17, 18]. The APDM Opal wireless sensors are positioned directly on the participant’s skin at the sacrum, laterally on each upper and lower leg, and each foot (Fig. 3). The wireless sensors are located at specific body landmarks. As shown in Fig. 3, the lumbar sensor is centered on the low back, at the base of the spine, and between the right and left posterior-superior iliac spines. The upper legs’ sensors are placed on the side of the thigh, midline, and 6 in above the femoral condyles. The lower leg’s sensors are located 2 in below and medial to the tibial tuberosity. The top medial corner of each foot sensor is placed at the intersection of the anterior tibialis tendon and the half-length of the shoe. Each of the seven sensors is secured with double-sided skin tape to limit displacement. IMUs are configured for synchronized logging at 128 Hz.

**Fig. 3 Fig3:**
[figure not shown]
APDM Opal Sensors Placement. IMUs (inertial measurement units), LC (lateral condyle), TT (tibial tuberosity), TAT (tibialis anterior tendon), SL (shoe length)

Before starting the walking assessment, participants are instructed to assume a neutral standing posture for 10 s and walk for approximately 2 min. Next, participants are instructed: “When ready, stand against this wall and place your feet in line with the tape arrows. Ensure your heels, back, and head are resting against the wall with your hands resting on your sides. Hold this position for about 10 seconds. Then, begin walking at the usual, comfortable walking speed. Next, turn and continue walking at a normal pace back and forth for 2 minutes. I will say STOP when the test is complete, then please take a seat.” During the testing, participants are instructed to “keep walking at your normal pace.” As shown in Table 4, the spatiotemporal metrics of gait (*r* > 0.86; ICC > 0.90) and gait kinematics (*r* > 0.7; ICC > 0.75) measures used in this study demonstrated excellent and good test-retest reliability, respectively [35].

**Table 4 Tab4:** Reliability of outcome measures

Reliability		*r*	ICC
Isometric strength	Hip extension (Nm)	0.74	0.85
	Hip flexion (Nm)	0.92	0.96
	Knee extension (Nm)	0.94	0.96
	Knee flexion (Nm)	0.95	0.97
	Ankle plantarflexion (Nm)	0.92	0.94
	Ankle dorsiflexion (Nm)	0.91	0.96
Gait			
Spatiotemporal metrics	Cadence (steps/min)	0.97	0.98
	Gait speed (m/s)	0.86	0.93
	Foot strike angle (degrees)	0.93	0.96
	Stance (%)	0.97	0.99
	Stride length (m)	0.95	0.98
	Swing (%)	0.97	0.99
Kinematics	Hip flexion (degrees)	0.70	0.82
	Hip extension (degrees)	0.70	0.82
	Knee flexion (degrees)	0.71	0.77
	Knee extension (degrees)	0.82	0.86
	Ankle plantarflexion (degrees)	0.94	0.95
	Ankle dorsiflexion (degrees)	0.93	0.93
Balance	Composite equilibrium score (%)	0.87	0.67

*r* Pearson’s correlation, *ICC* intraclass correlation coefficient

The assessment of gait includes six spatiotemporal parameters: cadence [steps/min], speed [m/s], foot strike angle [degrees], stance percent [% of gait cycle time GCT], stride length [m], and swing percent [% of GCT]. In addition, the assessment of gait includes the sagittal plane kinematics (range of motion ROM) of three lower extremity joints: hip flexion-extension ROM [degrees], knee flexion-extension ROM [degrees], and ankle dorsiflexion-plantarflexion ROM [degrees]. Preprocessing of raw data and extraction of spatiotemporal gait variables and joint ROM are performed using APDM’s mobility lab software (Version 1). The mobility lab software computes the mean and standard deviation for each gait outcome variable from approximately 50–60 gait cycles collected during gait assessment. After testing, the mobility lab software automatically generates a report in CSV format containing the mean and standard deviation for each outcome variable. The CSV files are then imported to the REDCap database for further statistical analysis.

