### Outcomes

The primary outcome is to assess the effects of exercise on gait, balance, and lower extremity muscle strength in 312 women randomized to either a 16-week home-based gait/balance intervention or an attention control educational cancer survivorship condition. The gait assessment includes spatiotemporal metrics (cadence, speed, foot strike angle, stance percent, stride length, and swing percent) and lower extremity joint kinematics (hip, knee, and ankle joint angles). The APDM Opal (Mobility lab v1, APDM, Inc., Portland, OR) inertial measurement units (IMU) system assesses gait. The APDM IMUs are wireless sensors for measuring motion that allows clinicians to perform gait assessments quickly and straightforwardly [17, 18]. Balance is assessed using the Sensory Organization Test (SOT) performed using a NeuroCom Balance Master (NeuroCom International Inc, Clackamas, OR) and the EquitTest System (v8.0). The SOT measures the participants’ ability to effectively use visual, vestibular, and somatosensory information to maintain balance. The SOT equilibrium score has demonstrated moderate to excellent test-retest reliability in healthy older adults and individuals with Parkinson’s disease [19–21]. Isometric strength of hip, knee, and ankle flexor and extensor muscles is assessed using an isokinetic dynamometer, Biodex BX Advantage (Biodex Medical Systems, Shirley, NY, USA), and the computer software program version 3.29 and 3.30 [22–25]. We also assess neuropathy symptoms using the FACT-Taxane Additional Concerns Subscale and nerve conduction velocity of the sural and peroneal nerve action potentials [26, 27]. Different outcomes will be analyzed separately. Multiple comparison methods such as the Bonferroni-Holm Method will be applied to control family-wise error rates.

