### Data analysis

Univariate descriptive statistics will be used to describe the characteristics of the sample, gait, balance, and lower extremity muscle strength. Values for the exercise will be divided into quartiles to determine the uppermost and lowest values to compare with published literature [43]. Analysis of univariate statistics allows us to assess the normality of distributions for our continuously distributed variables, patterns of missing values, and whether univariate outliers may be present that could distort subsequent bivariate and multivariate analyses. By implementing appropriate link functions in the generalized linear model framework, distributional assumptions, such as normality and potential non-linearity, will be addressed. Potential non-normality may also be addressed by implementing robust estimation through Huber-White standard errors (i.e., “sandwich” estimators), also implementable in the generalized mixed model framework. We do not aggregate outcomes. Instead, we are looking at a specific change of each metric between baseline and 16 weeks and comparing study groups. In addition, we will perform baseline comparisons between groups. Any unbalance covariate(s) will be adjusted in multivariate analyses. We do not plan any subgroup analyses.

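### Stance percent and swing percent are complements, so testing both as primary gait metrics reports one result twice (minor)

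*Protocol article*

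**What the plan says.** The protocol article's Outcomes section makes gait part of the primary outcome: "The primary outcome is to assess the effects of exercise on gait, balance, and lower extremity muscle strength in 312 women". It then lists the gait metrics, with stance and swing both among them: "The gait assessment includes spatiotemporal metrics (cadence, speed, foot strike angle, stance percent, stride length, and swing percent". Assessment of gait repeats the list as a count, "The assessment of gait includes six spatiotemporal parameters", and gives the units: "foot strike angle [degrees], stance percent [% of gait cycle time GCT], stride length [m], and swing percent [% of GCT".

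On analysis, Outcomes states "Different outcomes will be analyzed separately" and "Multiple comparison methods such as the Bonferroni-Holm Method will be applied to control family-wise error rates". Data analysis adds "We do not aggregate outcomes" and "we are looking at a specific change of each metric between baseline and 16 weeks and comparing study groups".

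The article does not rank the gait metrics, choose between stance and swing, or mention that one determines the other. It also does not say which outcomes form the family for the multiplicity adjustment, or how many there are.

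**The concern.** Two variables that sum to a constant are one measurement. If both are listed as primary gait metrics and each is compared between groups, a shift in stance time, real or by chance, appears a second time as a shift in swing time. No single gait metric is named as primary, so a reader may well look at how many of them moved, and two concordant rows would look like support for each other. The duplicate also takes a place in the multiplicity adjustment without adding information.

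**Working it through.** **1. The identity.** Both metrics are shares of gait cycle time (Assessment of gait). The cycle consists of stance and swing, so for the same leg swing % = 100 − stance %. The article does not print this; it follows from the terms. The analysed value is a mean over about 50–60 cycles, and the mean of (100 − x) is 100 − mean(x), so averaging preserves it. I assume both metrics come from the same leg, or are averaged over the same legs.

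**2. What the two tests give.** Change in swing = −(change in stance) for every participant. With an identity link, the two group differences are equal and opposite, with the same standard error and the same two-sided p-value. This also holds with adjustment for the metric's own baseline and with sandwich standard errors.

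**3. Size of the family (assumed).**
- Gait only: 6 spatiotemporal + 3 joint ranges of motion = 9.
- All primary domains: 6 + 3 + 1 balance + 6 strength = 16.
- Rows of Table 4: 6 + 6 + 1 + 6 = 19.
- Rows of Table 4 with strength kept separate by leg: 19 + 6 = 25.

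**4. The plan's own power figure.** Sample size states power .81 for a standardized effect of 0.30, with alpha .05 for one outcome. The plain two-group formula is Φ(d√(n/2) − z). With n = 156 per arm, 0.30 × √78 = 2.650, and Φ(2.650 − 1.960) = 0.755; with 20% lost it is 0.659. With baseline adjustment and 20% lost, it is 0.781 at a baseline correlation of 0.5 and 0.842 at 0.6. So .81 is attainable but cannot be confirmed, because the scale of the standardized effect is not given. This point disputes no stated figure and uses only the difference in power with and without the duplicate.

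**5. First Holm step for another metric** (d = 0.30, all 312, unadjusted). For m = 16: Φ(2.650 − 2.955) = 0.380 at .05/16, and 0.388 at .05/15.

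| m | α/m | α/(m−1) | Power, both tested | Power, one tested | Loss (points) |
|---|---|---|---|---|---|
| 9 | .005556 | .006250 | 0.451 | 0.466 | 1.5 |
| 16 | .003125 | .003333 | 0.380 | 0.388 | 0.8 |
| 19 | .002632 | .002778 | 0.360 | 0.366 | 0.6 |
| 25 | .002000 | .002083 | 0.330 | 0.334 | 0.4 |

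With 20% attrition, power goes from 0.279 to 0.286 at m = 16 when one of the pair is removed.

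**6. Later Holm steps.** With both tested and m = 16, once the pair is rejected 14 hypotheses remain if nothing else has been rejected, and the next threshold is .05/14. With one tested and m = 15, rejecting it also leaves 14, so the threshold is again .05/14. Other metrics pay only while the pair is unrejected.

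**7. Simulation of Holm** (300,000 replicates, m = 16, swing the exact negative of stance, compared with the same family without swing).
- All nulls true: both rejected in 0.32% of replicates, exactly one in 0.00%.
- Two or more false positives: 0.41% with the duplicate and 0.13% without, other outcomes independent; 0.70% and 0.48% at correlation 0.3.
- Family-wise error: 4.6% with and 4.9% without (independent); 4.2% and 4.5% at correlation 0.3.
- Power for another metric (independent case): 0.382 with and 0.390 without if only that metric has an effect; 0.453 and 0.463 if all do.

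**The case against.** The best defence is that the article never says both metrics enter the adjusted family. Bonferroni-Holm is named only as an example, and the membership of the family is commonly left to an analysis plan that is not shown. The primary outcome could also be read as three domains, with the metric list describing only what the equipment records. This stands as a limit: the double test is the natural reading of separate, unaggregated comparison of each metric, not an explicit statement. It does not remove the point, because the metric list and the rule of comparing each metric are both fixed in this text.

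It is also fair that no success rule counts significant metrics. The double reading is therefore a risk of interpretation and not a flaw in a decision rule.

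Several stronger readings are tempting and are not supported:
- *The duplicate inflates family-wise error.* It does not. Holm is valid under any dependence, and here it becomes slightly conservative.
- *Every other metric always faces a tighter threshold.* Step 6 of the working shows that the cost vanishes once the pair is rejected.
- *Table 4 proves the identity because both rows read r 0.97 and ICC 0.99.* The match is consistent with it but proves nothing: hip flexion and hip extension also share identical values (0.70 and 0.82).
- *The p-values must be identical under any analysis.* Data analysis allows other link functions. Under a log link, for example, a variable and 100 minus it need not give the same test.
- *Speed is redundant too, leaving about four independent gait quantities.* Speed is roughly stride length × cadence / 120, but it is not a linear function of either, and a product of means is not the mean of products. Its test can differ from both, and the count of four is not derived from anything in the document.

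**Conclusion.** The point holds, and it is minor. Stance percent and swing percent carry one piece of information but are listed as two primary gait metrics, with nothing to say that only one is tested. If both are tested with an identity link, they give one result twice. Error control is unharmed. The first-step power cost to other metrics is about 0.4 to 1.5 percentage points over assumed families of 25 down to 9 outcomes.

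This rests on three assumptions: that both percentages refer to the same leg or legs, that both enter the adjusted family, and that the model uses an identity link. Under another link the p-values may differ, but the information would still be duplicated.

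**What to change.** In Outcomes and in Assessment of gait, name one of the pair (for example stance percent) as the tested metric. State that swing percent is its complement and is either reported descriptively or dropped. Count the pair once when the multiplicity family is defined.

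The cost is one line in the outcome list. No data are lost, since swing percent can be recovered as 100 − stance percent. The choice should be recorded before any group comparison is seen. Trial status reports 33 participants recruited at the time of this version, so it could still be made as a prespecification.
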